# The effects of exercise during pregnancy on the newborn’s brain: study protocol for a randomized controlled trial

**DOI:** 10.1186/1745-6215-13-68

**Published:** 2012-05-29

**Keywords:** Event-related potentials, Exercise, Mismatch negativity, Newborn, Pregnancy

## Abstract

**Background:**

It is generally accepted that an active lifestyle is beneficial for cognition in children, adults and the elderly. Recently, studies using the rat animal model found that the pups of mothers who exercised during pregnancy had increased hippocampal neurogenesis and better memory and learning abilities. The aim of this report is to present the experimental protocol of a study that is designed to verify if an active lifestyle during pregnancy in humans has an impact on the newborn's brain.

**Methods:**

60 pregnant women will be included in a randomized controlled study. The experimental group will be asked to exercise a minimum of 20 minutes three times per week, at a minimal intensity of 55% of their maximal aerobic capacity. The control group will not be exercising. The effect of exercise during pregnancy on the newborn's brain will be investigated 8 to 12 days postpartum by means of the mismatch negativity, a neurophysiological brain potential that is associated to auditory sensory memory. We hypothesize that children born to mothers who exercised during their pregnancy will present shorter latencies and larger mismatch negativity amplitudes, indicating more efficient auditory memory processes.

**Discussion:**

As of September 2011, 17 women have joined the study. Preliminary results show that the experimental group are active 3.1 ± 0.9 days per week while the control group only exercise 0.8 ± 0.6 days per week. The results of this study will present insight on fetal neuroplasticity and will be a valuable tool for health professionals who wish to encourage pregnant women to exercise.

**Trial registration:**

ClinicalTrials.gov registration: NTC01220778

## Background

Accumulating data supports that an active lifestyle is beneficial for cognitive functioning in children [1-3], adults [4] and the elderly [5]. For example, Davis *et al.*[6] found that 7- to 11-year-old children who exercised 40 minutes per week for 15 weeks performed significantly better on a test of executive functions than children who exercised for 20 minutes or less.

A recent group of studies using various exercise protocols with the rat animal model also suggests that maternal exercise during pregnancy has a beneficial influence on the development of the fetal brain that ultimately leads to functional changes for the newborn rat pups [7-14]. Parnpiansil *et al.* report that the pups of mothers who exercised during pregnancy had increased hippocampal neurogenesis as well as better memory and learning abilities. Specifically, 30 minutes of treadmill running five days per week during gestation was associated with better spatial learning in the multiple t-maze [8]. Further, Akhavan *et al.* found that both voluntary running and forced swimming during gestation increased the quantity of cells in the cornus ammonis 1 (CA1) and dentate gyrus regions of the hippocampus of the rat pups and facilitated learning in the Morris Water Maze [12].

Few studies with humans have investigated the relationship between physical activity during pregnancy and the offspring’s cognitive functioning. In a series of seminal studies, Clapp and his team compared the children of women who continued to be active during their pregnancy to those of closely matched women who voluntarily stopped exercising during their pregnancy. All participants were recruited before their pregnancy and their exercise performance, dietary intake, weight gain and physiologic responses were monitored throughout their pregnancy. The active women ran, performed aerobics or cross-country skied three or more times a week for 20 minutes or more at an intensity above 55% of their maximal aerobic capacity (VO_2_max). Five days after their birth, the offspring of the mothers who were active during their pregnancy scored higher on the orientation and state regulation subscales of the Brazelton Neonatal Behavioral Assessment Scales. This reflects the ability to orient to stimuli from the environment and the ability to self-regulate after the presentation of sound and light stimuli [15]. Further, in a separate study, at the age of one year, the children of the active group had a significantly higher score on the psychomotor scale of the Bayley Scales of Infant Development [16] and, in yet another study, at the age of five years old they had better results on tests of general intelligence and oral language [17]. Important as they may be, these studies do have some notable limitations that need to be considered in the interpretation of their results. First, no direct measure of brain or neuronal change is provided. The data from the neonates suggest that exercise during pregnancy influences certain of the newborns’ behaviors, but unlike the data from the animal studies they do not provide direct evidence of changes in brain activation. Second, the results of the two older age groups could have been influenced by differences in the upbringing provided by the mothers from each group. As acknowledged by Clapp and his team, ‘perhaps there is something fundamentally different about the maternal-child interaction in the families of the women who chose to maintain their exercise throughout pregnancy’ [17]. The goal of the present study was to extend the work of Clapp and his colleagues by comparing the neurophysiological brain potentials of babies born to women who were active during their pregnancy to those of babies born to women who were sedentary.

Recent studies in humans have been able to directly investigate functional neural activation in newborns by means of the mismatch negativity (MMN), a component of the auditory event-related potential [18,19]. The MMN wave is elicited by presenting a rare auditory stimulus in a series of repetitive frequent standard sounds. The MMN has been associated with auditory sensory memory and several authors believe that it is an objective measure of the newborn’s cognitive status [20]. For example, earlier and stronger MMN waveforms indicate greater developmental maturity [21], whilst a longer latency and a smaller amplitude are associated with slowed development in children with cleft palate [22] or autism [23].

To further our understanding of the effects of exercise during pregnancy on the development of the human brain, we propose to use a randomized intervention protocol and a direct measure of neonatal brain functioning. Pregnant women will be randomly allocated to an active group or an inactive control group and the latency and amplitude of the MMN evoked-potential will be recorded in their newborns. Given that the main finding from animal studies is an improvement in learning and memory in the offspring of active mothers, we hypothesize that children born to mothers who exercised during their pregnancy will present shorter latencies and larger MMN amplitudes compared with babies born from non-exercising mothers.

## Methods

### Design and ethical considerations

This will be a single-center randomized controlled trial with a two-group design: one group exercising regularly and a non-exercising control group.

All study procedures have been approved by the Health Sciences Research Ethics Committee of the University of Montreal, Montreal, Quebec, Canada. Informed consent will be obtained after participants receive verbal and written information about the purpose and procedures involved in the study and before any data collection begins.

### Recruitment and participants

All obstetricians and gynecologists of the Montreal area were contacted with the help of the Collège des Médecins du Québec and were asked to distribute brochures to women who meet the inclusion criteria. Advertisements were also placed on Facebook and articles were published in the university paper and on several specialized blogs. Recruitment will continue until 60 pregnant women have joined the study, 30 in the exercise group and 30 in the control group.

Inclusion and exclusion criteria were chosen to minimize individual differences among participants and to ensure the women’s safety (see Table1). Participants will be withdrawn from the study if exclusion criteria are met during the course of the study or if they withdraw their consent.

**Table 1 T1:** Inclusion and exclusion criteria for the Healthy Mom, Bright Child study

**Inclusion criteria**	**Exclusion criteria**
First trimester of pregnancy	Use of alcohol, cigarettes or illegal drugs
20 to 35 years of age	Health complications
Pre-pregnancy body mass index between 18 and 25	Unable or unwilling to breastfeed
No known health conditions	Excessive or insufficient weight gain (25 to 35 lbs according to pregnancy weight gain recommendations) [24]
Use of folic acid	Non-compliance with the experimental protocol

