**Figure 1 F1:**
[figure not shown]
Study design.

Two interventions will be offered: individual recommendations on health habits during pregnancy; and individual recommendations on exercising during pregnancy. To ensure that each group has similar knowledge about health habits during pregnancy and that there is the same amount of one-on-one contact with all participants, both groups will receive the first intervention. Only the active group will receive the second intervention, recommending at least three sessions of exercise per week (see section on Exercise intervention). Participants in the control group will not be given any exercise counseling and will be informed they will be excluded from the study if they exercise more than once per week.

Starting at the beginning of the second trimester, all women will complete a daily log and wear a pedometer for the entire duration of the study. Women from both groups will meet monthly with the same kinesiologist and will receive standardized advice and feedback based on their daily log. During that meeting, all the women will complete a mood questionnaire and the women who are part of the active group will complete an exercise session in order to learn how to characterize their at-home exercise for the daily log. The women who are part of the control group will complete the same exercise session but only once per trimester. During each trimester women from both groups will fill out a three-day nutrition journal and during the second and third trimesters they will wear an accelerometer and a Polar heart rate monitor for seven days and three nights. The timeline of the experimental protocol is presented in Figure2.

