### Medical records

A copy of the complete medical records will be obtained from each woman’s obstetrician at the postnatal visit to verify weight gain and standard pregnancy blood test results as well as details of the delivery.

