### Methodological strengths

There are several strengths to the proposed protocol. First, we use validated and sensitive neuroelectric measures of the newborn’s brain activity. Also, the prospective randomized design will ensure that the participants in the active and the control groups are comparable for all other characteristics. We will verify group parity by comparing sociodemographic status, pre-pregnancy health status, pre-pregnancy and first trimester KPAS scores, nutrition journals, and scores on the anxiety scale. Further, the same kinesiologist will meet with all of the participants to ensure the standardization of the experimental protocol, including advice and feedback.

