### Methodological weaknesses

Our protocol also has some limitations that will be taken into account in the interpretation of the data, but that are unlikely to influence the overall pattern of results. Our close monitoring of the participants’ daily exercise via the daily log and wearing of a pedometer will allow us to determine the amount of exercise completed by the experimental group and will allow us to eliminate members of the control group who do not conform to the non-exercising criteria.

We are aware that the MMN is not an intuitive measure for parents about the general functioning of their newborn. However, there are several reasons why we opted for this measure. First, although it may seem abstract, it is associated with specific behavioral processes including sensory memory and cognitive status [18-20]. Second, it is an objective measure of brain functioning in the newborn that is not subject to examiner bias or the child’s state of wakefulness [19]. There are no known behavioral equivalents to this measure that are as sensitive to the newborn’s brain functioning.

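### Randomised women are withdrawn for non-compliance, control-arm exercise or weight gain, so selection bias can enter the comparison of newborn brain responses after allocation

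*Protocol article*

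**What the plan says.** Under Recruitment and participants, the exclusion criteria stay in force after enrolment: "Participants will be withdrawn from the study if exclusion criteria are met during the course of the study". The wording is withdrawal from the study, not from the intervention. Table 1 lists among these criteria "Non-compliance with the experimental protocol" and "Excessive or insufficient weight gain (25 to 35 lbs according to pregnancy weight gain recommendations".

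Procedure and timeline adds a rule for one arm only. Control women "will be informed they will be excluded from the study if they exercise more than once per week". Methodological weaknesses presents this as an advantage: monitoring "will allow us to eliminate members of the control group who do not conform to the non-exercising criteria". Weight gain is checked from the obstetrician's records, obtained "at the postnatal visit to verify weight gain", which is after the intervention has ended.

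Two statements rest on randomisation. Procedure and timeline says that assigning women only after consent avoids self-selection. Methodological strengths says that "the prospective randomized design will ensure that the participants in the active and the control groups are comparable for all other characteristics". The Statistical analyses section describes the ANOVAs without naming an analysis of all women as randomised.

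**The concern.** Non-compliance and gestational weight gain can be seen only after allocation. Staying compliant requires regular exercise in the active arm and near-absence of exercise in the control arm. Removing non-compliers can therefore keep women with a high tendency to exercise in one arm and women with a low tendency in the other. If that tendency, or a maternal trait linked to it, relates to the newborn's MMN, a difference appears without any effect of exercise during pregnancy. Weight gain is a separate route, because exercise may change it, and conditioning on it then selects differently by arm.

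Consent before assignment protects only the moment of allocation. A woman withdrawn before the day 8 to 12 recording leaves no MMN, so no later choice of analysis set can bring her back.

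**Working it through.** **1. The plan's own figure.** Sample size calculations gives a difference of 50%, SD 56%, alpha 0.05 and power 80%. The standardised difference is 50/56 = 0.893. A two-sided two-sample t-test needs 20.7, rounded up to 21 per group (power 80.6% at 21), and 21/0.70 = 30. The stated 21 and 30 reproduce. The arithmetic is sound, and it budgets for losing 30% of randomised women.

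**2. Removals so far** (Preliminary results). Of 17 randomised women, 5 were excluded: two miscarriages, one twin pregnancy, one withdrawn consent and one non-compliance. So 1 of 17 (5.9%) reflects the rules at issue.

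**3. Scenario model.** There is no true effect, 30 women are randomised per arm, and one MMN amplitude per infant (SD 56%) is compared by t-test. Exercise tendency is standard normal and correlates r with MMN within each arm. The r values of 0.2 and 0.3 are assumptions. If a fraction p is removed from one tail at cut-point z, the retained mean shifts by m = φ(z)/(1 − p), and the false difference is 56 × r × (m in active + m in control). The filters act in opposite directions.

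- *1/17 removed in each arm:* m = 0.117/0.941 = 0.125 per arm. At r = 0.2: 56 × 0.2 × 0.25 = 2.8 points. At r = 0.3: 4.2 points.
- *Control rule only:* with the reported 0.8 ± 0.6 days/week and normality, P(more than 1) = P(Z > 0.333) = 0.369 and m = 0.377/0.631 = 0.598. The false difference is 6.7 (10.1) points.
- *Hard cut-offs in both arms:* in addition, with 3.1 ± 0.9 days/week, P(fewer than 3) = P(Z < −0.111) = 0.456 and m = 0.396/0.544 = 0.729. The sum is 1.327, giving 14.9 (22.3) points. About 16 active and 19 control women would remain of 30 each.

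Simulated type I error, nominal 5%; ranges show variation between simulation runs:

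| Scenario | r = 0.2 | r = 0.3 |
|---|---|---|
| 1/17 removed per arm | 5.3% | 5.8–5.9% |
| Control rule only (37% removed) | 6.5–6.9% | 9.2–9.3% |
| Hard cut-offs, both arms | 12% | 21–22% |
| r = 0, any of the above | about 5% | – |

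If selection ran in the same direction and to the same extent in both arms, the bias would cancel and type I error would stay near 5%.

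**4. Weight gain.** The article gives no mean or SD. If the mean were 30 lb, the fraction outside 25 to 35 lb is 2 × P(Z > 5/SD): 30% at SD 4.8, 53% at SD 8 and 68% at SD 12. The mean and all three SDs are assumptions, so the removal rate is unknown.

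**The case against.** The strongest reply is that the rules as operated do little. One woman in 17 was removed for non-compliance, and at that rate the false difference is 3 to 4 points and type I error barely moves. This stands as a limit on size. One event in 17 is imprecise, however, and the rule remains in force for the rest of recruitment.

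A reader might infer several stronger things that the document does not support.

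- *That 46% of active women and 37% of controls will be lost.* The means and SDs behind those figures come from the 7 and 5 women already retained, so applying the cut-offs to them filters the same women twice. No removal threshold is stated for the active arm. Three sessions a week is what those women are asked to do, and only controls have an explicit limit.
- *That Table 2, which shows 12 of the 17 women, demonstrates the selection.* Four of the five exclusions were miscarriages, a twin pregnancy or withdrawn consent. The split of 2 of 9 against 3 of 8 is too small to show differential loss.
- *That the breastfeeding criterion ("Unable or unwilling to breastfeed") biases the comparison.* It too can operate after allocation, but nothing shows that it works differently by arm.
- *That the trial recreates the flaw the Background finds in earlier work.* That criticism concerns upbringing in the two older age groups. For newborns the complaint was the lack of a direct brain measure.

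A statistical analysis plan, not shown here, might define an intention-to-treat set. It could not supply recordings that were never made.

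**Conclusion.** The point holds as a defect in a stated rule. The plan removes randomised women from the study for events that follow allocation. The control-exercise rule is arm-specific, non-compliance means different behaviour in each arm, and weight gain may be affected by exercise. Selection bias can therefore return, and the claim that randomisation ensures comparable groups does not hold for the retained women.

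The size and direction of the bias cannot be derived from the document. The scenarios run from about 3 to about 22 of the 50 planned percentage points, with type I error between about 5% and 22%. They rest on the assumed correlations, normality, opposite-direction filters and adherence figures from 12 retained women. It would go too far to say that the error rate is known to be inflated. It should still be corrected now, because recruitment is ongoing and a missed newborn recording cannot be obtained later.

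**What to change.** Separate stopping the intervention from leaving the study. Do not use non-compliance, control-arm exercise, weight gain or breastfeeding as grounds for removing a randomised woman from follow-up or from the primary analysis. Record the day 8 to 12 EEG for every live-born infant whose mother still consents. Make the analysis by allocated arm primary, and report the compliant subset as a labelled secondary per-protocol analysis. Show all randomised women in the baseline table. Rules on safety and on stopping the intervention are untouched by this change.

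The cost is revised wording, a few more newborn EEGs and some dilution of the effect, so power should be restated. The dilution fractions below are assumptions (two-sided t-test, SD 56%, all 30 per arm analysed, before unavoidable losses):

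| Dilution | Difference | Power at 30 per arm | Per arm for 80% |
|---|---|---|---|
| 0% | 50% | 92.5% | 21 |
| 10% | 45% | 86.4% | 26 |
| 20% | 40% | 77.6% | 32 |
| 30% | 35% | 66.3% | 42 |

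The planned 30 per arm keeps 80% power at 10% dilution but not at 20%.

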### General information questionnaire

During the first visit, all participants will be asked to answer questions regarding their and their partner’s professional, economic, educational and health status as well as a family history of hereditary disorders. This questionnaire also documents the details of the participants’ pregnancy.

Monthly visits will include a follow-up questionnaire that will inquire about their health and general habits (for example, alcohol consumption, massages, acupuncture) to ensure they remain eligible to participate in the study as well as to document potential confounders between the two groups.

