### Preliminary results

As of September 2011, 17 women have given their consent and been randomly assigned to one of the two groups: nine in the exercise group and eight in the control group. Two women from the exercise group and three from the control group were excluded: two for having a miscarriage, one for being pregnant with twins, one for not complying with the experimental protocol, and one for withdrawing consent. Table2 presents the characteristics of all participants.

**Table 2 T2:** Participant characteristics

	**Active group**	**Control group**
	**(n = 7)**	**(n = 5)**
Age (years)		
Mother	29 ± 3	28 ± 4
Father	31 ± 4	31 ± 6
Pre-pregnancy body mass index	24.9 ± 3.7	27.9 ± 5.8
Pre-pregnancy KPAS index	11.62 ± 1.39	10.93 ± 0.65
First trimester KPAS index	9.71 ± 1.19	8.97 ± 1.39
Mother	3 (3)	5 (5)
Father	5 (7)	3 (3)
Revenue ($)	80,000 to 100,000	60,000 to 80,000
(median class)	(40,000)	(40,000)

Data presented as the mean ± standard deviation, except for Education and Revenue, which are presented as the interquartile range. KPAS: Kaiser Physical Activity Survey.

Preliminary results indicate that all women completed the online daily log from week 13 until birth. The active women (n = 7) had journal entries for 23 to 28 weeks and exercised an average of 3.1 ± 0.9 days per week. Sessions lasted from 20 to 90 minutes, at an intensity ranging from 12 to 15 on the Borg scale. Activity type included aerobics, swimming, tennis, elliptical training, hiking, circuit training, Wii sports and rollerblading, with the most common being walking, cycling and water aerobics. Women in the control group (n = 5) had journal entries for 24 to 27 weeks and exercised an average of 0.8 ± 0.6 days per week. Sessions lasted from 20 to 40 minutes, at an intensity ranging from 12 to 13 on the Borg scale. Activities included cycling, water aerobics and swimming, walking being by far the most common.

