#### Statistical analyses

A series of analyses will be completed to determine parity between the groups. Specifically, t-tests will compare sociodemographic status, pre-pregnancy health status, pre-pregnancy and first trimester KPAS scores, nutrition journals, and scores on the anxiety scale between the control and the active groups. We will also complete a qualitative analysis of the medical records including standard blood test results and the details of delivery. A second series of t-tests will verify compliance with the experimental protocol by comparing the data from the daily exercise logs, the pedometers and the accelerometers of both groups.

Separate repeated measure analysis of variance (ANOVA) will be performed on the amplitude and latency data of the recorded brain waves. For each ANOVA, the between-subject factor will have two levels, corresponding to the exercise and control groups and the within-subject factors will be region (frontal, central and parietal) and laterality (left, central and right). Statistical analyses will be carried out using the SPSS software (SPSS 17.0, Chicago, IL, USA). A *P* <0.05 will be considered statistically significant.

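### A health complication after randomisation takes a woman out of the study, and not only out of her assigned exercise or restriction, so her later pregnancy, delivery and newborn outcomes may be lost

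*Protocol article*

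**What the plan says.** Recruitment and participants fixes what happens when a criterion is met after entry: "Participants will be withdrawn from the study if exclusion criteria are met during the course of the study or if they withdraw their consent". One of the exclusion criteria in Table 1 is simply "Health complications", with no definition or grading. The same section gives the reasons for the criteria: "Inclusion and exclusion criteria were chosen to minimize individual differences among participants and to ensure the women’s safety". It does not separate stopping the assigned activity from leaving follow-up.

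Three other sections bear on what is still collected:

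- **General information questionnaire.** The monthly health questions are asked "to ensure they remain eligible to participate in the study as well as to document potential confounders between the two groups".
- **Medical records.** "A copy of the complete medical records will be obtained from each woman’s obstetrician at the postnatal visit". The section does not say whether this includes a woman already withdrawn.
- **Statistical analyses.** Within the paragraph on group parity: "We will also complete a qualitative analysis of the medical records including standard blood test results and the details of delivery".

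Preliminary results shows exclusions in practice. Of 17 women randomised (9 exercise, 8 control), 5 were excluded: 2 from exercise and 3 from control. The reasons were two miscarriages, one twin pregnancy, one case of non-compliance and one withdrawal of consent. They are pooled over the arms.

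**The concern.** A complication that arises after randomisation is an event that exercise, or its restriction, could influence. A rule that ends follow-up at that event selects on something that happens after allocation. The women whose later course matters most for the safety record are then the ones whose course may go unrecorded, and the two arms may lose different numbers.

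Neither stated reason for the criteria calls for this. Safety justifies ending the exercise or the restriction. Keeping participants alike is a reason to select women at entry; it does not require dropping a randomised woman because of what happened to her later.

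The stake is modest but real. The Discussion makes no safety claim, but it expects a positive result to lead health professionals to promote exercise in pregnancy for the child's sake. A reader of that message would want to know how pregnancies and deliveries went for all the women randomised.

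**Working it through.** **1. The plan's own figures.** Inputs from Sample size calculations: difference 50%, SD 56%, alpha 0.05 (two-sided reproduces the result), power 80%, attrition 30%. The standardised difference is 50/56 = 0.893. The two-sample t-test needs 20.7, rounded up to 21 per group, and 21/(1 − 0.30) = 30 enrolled. The plan's figures reproduce and are not in dispute. They matter here only because they set the number of withdrawals the plan expects.

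**2. What is known about a withdrawn woman, section by section.**

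| Information | Where | Status |
|---|---|---|
| The complication that triggers withdrawal | General information questionnaire; Preliminary results | Known: it must be seen before it can trigger withdrawal, and exclusions to date are logged with arm totals and reasons |
| Her later pregnancy, delivery and newborn health | Medical records | Open: the text may or may not extend to withdrawn women |

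**3. Why the second row is open.** The Medical records wording could cover everyone. But when the article speaks of everyone in Preliminary results, it means the retained women:

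- "Table2 presents the characteristics of all participants", yet Table 2 has 7 + 5 = 12 women of the 17 randomised.
- "Preliminary results indicate that all women completed the online daily log from week 13 until birth", which cannot include the two women who miscarried.

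If the Medical records section uses the same convention, withdrawn women have no record. If it does not, they do. The article does not settle this.

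**4. What the exclusions to date can and cannot show.** 5/17 = 29.4% (Clopper-Pearson 95% interval 10.3% to 56.0%). This is the rate of exclusion for any reason. The twin pregnancy, the non-compliance and the withdrawn consent are not shown to be health complications, and no later follow-up is reported for any of the five. No rate of lost outcomes can be taken from it.

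**5. How often the rule could apply.** The documents give no complication rate. Under assumed rates of 5%, 10% and 20%, the rule would apply to 60 × 0.05 = 3, 60 × 0.10 = 6 and 60 × 0.20 = 12 women in the whole trial. The chance of at least one in an arm of 30 is 1 − (1 − p)^30 = 79%, 96% and over 99%. These are counts of women to whom the rule would apply, not of outcomes lost.

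**6. Ceiling on the cost of the remedy.** Planned attrition for any reason gives 0.30 × 60 = 18 withdrawn women; the rate to date gives 5/17 × 60 = 17.6. So there would be at most about 18 extra record requests, and none if withdrawn women are already covered.

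**7. What full records could show.** With no events in an arm, the upper 95% limit for the risk is 1 − 0.025^(1/n): 11.6% for n = 30 and 16.1% for n = 21. For assumed risks of 10% versus 20% with 30 per arm, Fisher's exact test (two-sided 0.05, by enumeration) has 9.6% power. Complete records give a fuller description; they do not separate the arms.

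**The case against.** The strongest reply is that most of this is silence in a condensed article. How withdrawn women's records are handled, and whether complications are tabulated by arm, are matters commonly left to a full protocol or an analysis plan, and neither is shown. The Medical records section exempts no one, and the wording of an interim description should not decide who is meant in a data-collection section. The triggering event is known to the study. The primary outcome is the MMN, and the proposed listing has almost no power to separate the arms.

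Much of this stands:

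- A reader might infer that complications go unrecorded. The documents do not support that: the monthly questionnaire and the logged exclusions show that the triggering event is captured.
- A reader might infer that withdrawn women certainly have no obstetric record. The text leaves this open in both directions.
- A reader might treat the lack of a planned table by arm as an error. It may be in a document not shown, so it is not counted as a fault here.
- A reader might take 29.4% as the size of the loss. It mixes unrelated reasons and says nothing about later outcomes.

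One thing is not answered. The withdrawal rule is a stated rule, not an omission. A later table cannot count events that were never collected, and the wish for similar participants does not justify ending follow-up once a woman has been randomised.

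**Conclusion.** The point holds as a minor one about conduct and the safety record. As worded, a health complication after randomisation ends a woman's participation in the study when it need only end her assigned activity. Her later pregnancy, delivery and newborn outcomes may then be missing, possibly to a different degree in each arm.

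The size of the loss cannot be estimated from the documents, and it may be small if records are already to be collected for withdrawn women. The conclusion rests on reading withdrawal from the study literally and on the assumption that no document outside the article separates stopping the activity from stopping follow-up. It does not touch the sample size, and it makes no claim about bias in the MMN comparison.

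**What to change.** 1. In Recruitment and participants, state that a health complication ends the assigned exercise or restriction but not follow-up.
2. In Medical records, state that the record is obtained for every randomised woman, including any who stop the assigned activity or are withdrawn, unless she refuses.
3. If complications are listed by randomised arm, present the listing as descriptive. Note for each event, including the two miscarriages already seen, whether it came before any exercise exposure: women join before week 13, the intervention is meant for the second and third trimesters, and the article gives neither the timing nor the arm of those miscarriages. Say plainly that 60 women cannot establish safety.

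The cost is two changes of wording, at most about 18 extra record requests, and a short listing if one is made. The downside is that consent must allow record access after the assigned activity stops, and some women will refuse. With 17 women randomised by September 2011 and recruitment ongoing, most of the 60 could still be covered.
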